### 2.6. Rescue Medication

Participants will be instructed not to take any medication that may influence IBS symptoms throughout the entire duration of the trial. However, in case of worsening symptoms, they are allowed to take painkillers such as paracetamol, paracetamol plus Hyoscine butyl bromide, antispasmodics, and loperamide, as rescue medication. All rescue medications will be recorded by the researchers.

### 2.7. Adverse Events, Serious Adverse Events, and Study Discontinuation

An adverse event (AE) is any undesirable or unfavorable medical occurrence in a participant or subject who is exposed to a medicine, a medical product, or an intervention like diet. An AE does not necessarily have a causal relationship with the medicine, product, or intervention. An AE can be any sign, symptom, or disease that is temporally associated with the use of the medicine, product, or intervention, whether or not considered related to it. An AE is serious and should be reported when the participant’s outcome is death, life-threatening, hospitalization, disability, or other significant impairment. All AEs will be recorded and causality association with treatment will be assessed. All serious adverse events (SAEs) will be reported according to the local legislation.

Participants can terminate their study participation at any time if they wish, or due to the occurrence of AE, progression, or intractable symptoms they are unable to control with the interventions and/or rescue medications. All discontinuations and their reason will be recorded.

### 2.8. Data Collection, Questionnaires and Evaluations

We will record demographic characteristics, such as age, sex, marital status, employment status, educational level, income and smoking habits from all subjects. Anthropometric data, such as weight, and height will be used to calculate the Body Mass Index (BMI) [weight (kg)/height^2^ (m^2^)] [19]. Participants with BMI < 18.5 kg/m^2^ are classified as underweight, 18.5 kg/m^2^ to <25 kg/m^2^ as normal, 25 kg/m^2^ to <30 kg/m^2^ as overweight and ≥30 kg/m^2^ as obese [20].

#### 2.8.1. Questionnaires

During the study periods, we will measure the severity of their symptoms using the IBS-SSS [21], which is validated in the Greek population [22], the general quality of life (QoL) using the 12-item Short Form Survey (SF12) questionnaire, which is commonly used [23,24] and validated in the Greek population [25], the IBS-associated quality of life using the Irritable Bowel Syndrome-Quality of Life Measure (IBS-QoL) [26,27], which has been validated in the past [28,29,30,31,32]. IBS burden symptoms will be measured using the Gastrointestinal Symptom Rating Scale-IBS version (GSRS-IBS) designed to assess gastrointestinal symptoms specifically for IBS participants [33]. The Hospital Anxiety and Depression Scale (HADS) questionnaire, validated in the Greek population [16], will be used to measure depression [HADS-D] and anxiety [HADS-A] separately [34]. Details regarding the aforementioned questionnaires are provided in Appendix B.

#### 2.8.2. Adequate Relief

Adequate relief (AR) is one of the most commonly used endpoint measures in IBS randomized controlled trials [35,36]. It will be evaluated with a single-item question, asking the participant: “In the last seven days, have you experienced adequate relief of your IBS symptoms?”. AR will be assessed through weekly telephone contact over four weeks for the NICE group and during the elimination reintroduction phases for the MED-LFD group. AR is achieved if positive answers are received in more than 50% of recordings within the given period. According to the study design, AR will be measured once after six months in both groups to evaluate symptom relief during the last week of follow-up.

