#### 2.4.2. Control Group

Participants in the control group will receive a weekly dietary plan for four weeks according to NICE guidelines for IBS participants [16], in which they may choose with free will foods from specific categories, i.e., vegetables, fruits, and grains. This includes regular meals, avoiding eating too little or too much, staying hydrated, reducing the intake of caffeine, alcohol, fizzy drinks, fatty, spicy, and processed foods, limiting fresh fruit intake to a maximum of three servings per day (approximately 80 g), high-fiber food (such as whole meal or high-fiber flour and bread, cereals high in bran, and whole grains such as brown rice), resistant starch, and sweeteners, and addressing any perceived food intolerances such as dairy [16]. An indicative analysis of the mean daily nutrition information of the NICE diet recommendation per week using https://explorefood.foodafactoflife.org.uk (accessed on 10 January 2024), is presented in Table 1.

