##### Second Phase

Participants experiencing adequate relief symptoms during phase 1 will proceed to phase 2. During this phase (reintroduction), which will last for 6 to 8 weeks, participants will determine their tolerance to individual FODMAP subgroups such as fructose, lactose, galacto-oligosaccharides, fructans, and polyols. In this phase, we will find out which FODMAPs can be tolerated by introducing only one FODMAP subgroup at a time, typically for three days, with three washout days in between subgroups introductions [18]. At this stage, participants will be encouraged to use a diary to identify trigger foods and to record symptom responses to set filters in the Monash FODMAP app during the third phase. Details regarding the Monash FODMAP app are provided in Appendix A.

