### 2.9. Study Timepoints

Three study timepoints are anticipated: Baseline: Two to four days before intervention initiation; first follow-up: at 4 weeks following the introduction of the dietary plan for the NICE group and at the end of the reintroduction phase for the MED-LFD group, anticipated to last on average 6–8 weeks (2–4 days’ time window); second follow-up: at six months (1-week time window), as shown in Figure 1, which also illustrates the procedures to be performed at each timepoint.

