### 2.10. Study Endpoints

The study’s primary endpoint is the change from baseline of IBS-SSS at the first and the second follow-up. The co-primary endpoint is the rate of responders for each dietary intervention, defined by a ≥50-point reduction in IBS-SSS, which has been shown to be a clinically significant improvement [21,37], at the first and second follow-ups. Secondary endpoints measured at both follow-ups will include the rate of subjects reporting AR and changes in IBS-QoL, SF-12, HADS, and GSRS-IBS. Adherence to dietary intervention, use of rescue medications, rate of participants who achieve IBS-SSS < 175, discontinuation rate (and causes), and AE/SAEs comprise also secondary endpoints.

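### Adequate relief at first follow-up is judged over four weekly calls in NICE but over a longer series in MED-LFD that includes reintroduction weeks, so the two rates are not comparable

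*Protocol article*

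**What the plan says.** Section 2.8.2 asks a single question about the past seven days ("In the last seven days, have you experienced adequate relief of your IBS symptoms"), so each recording covers one week. The collection period depends on the arm: "weekly telephone contact over four weeks for the NICE group and during the elimination reintroduction phases for the MED-LFD group". One rule then applies to both: "AR is achieved if positive answers are received in more than 50% of recordings within the given period". At six months, AR is one recording in each arm.

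The lengths come from other sections. Section 2.4.2 gives the NICE plan four weeks: "Participants in the control group will receive a weekly dietary plan for four weeks". For MED-LFD, the Second Phase text under 2.4.3 states: "During this phase (reintroduction), which will last for 6 to 8 weeks". It also says that only participants with adequate relief in phase 1 go on to phase 2. Section 2.9 places first follow-up for this arm "at the end of the reintroduction phase for the MED-LFD group, anticipated to last on average 6–8 weeks", which can be read as the length of reintroduction alone or as the total time. The article gives no length for the restrictive phase.

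Section 2.10 makes the AR rate an endpoint: "Secondary endpoints measured at both follow-ups will include the rate of subjects reporting AR". Section 2.11.3 compares categorical variables between the arms by chi-squared test, with p ≤ 0.05 regarded as significant.

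**The concern.** A rule of strictly more than half behaves differently for short and long series. With four calls it requires three positive answers, or 75%. With more calls the required share falls towards 50%, and a longer series also smooths out week-to-week variation. The same weekly experience can therefore be classified differently depending on the arm.

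The periods differ in content too. The MED-LFD series includes weeks in which FODMAP subgroups are deliberately reintroduced, and NICE has no counterpart. Entry to those weeks is itself conditional on relief in phase 1.

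At stake is the reading of a secondary endpoint in an open-label trial. A difference in AR at first follow-up, or its absence, could not be separated from the effect of the counting rule.

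**Working it through.** The plan gives no figure for AR, so there is none to reproduce. The check asks what AR rates two equally effective diets would show.

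**Inputs from the article:** strictly more than 50% of recordings; four recordings in NICE; reintroduction of 6–8 weeks; 54 participants per group.

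**Assumptions:** the same weekly chance p of a 'yes' in both arms, varied from 0.3 to 0.7; MED-LFD recordings k = 6 or 8 (if 6–8 weeks is the total) or 10 or 12 (if a four-week restrictive phase is added).

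**Step 1. Threshold.** The smallest qualifying count is m = floor(k/2) + 1. This gives 3 of 4 (75%) in NICE, against 4 of 6 (67%), 5 of 8 (62.5%), 6 of 10 (60%) or 7 of 12 (58%) in MED-LFD. Odd counts are lower still: 4 of 7 (57%), 6 of 11 (55%).

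**Step 2. Independent weeks, everyone contributes the full series.** P(AR) = P(Bin(k, p) ≥ m). For NICE at p = 0.6 this is 4 × 0.6³ × 0.4 + 0.6⁴ = 0.3456 + 0.1296 = 0.475.

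| p | NICE, k=4 | k=6 | k=8 | k=10 | k=12 |
|---|---|---|---|---|---|
| 0.3 | 8.4% | 7.0% | 5.8% | 4.7% | 3.9% |
| 0.4 | 17.9% | 17.9% | 17.4% | 16.6% | 15.8% |
| 0.5 | 31.2% | 34.4% | 36.3% | 37.7% | 38.7% |
| 0.6 | 47.5% | 54.4% | 59.4% | 63.3% | 66.5% |
| 0.7 | 65.2% | 74.4% | 80.6% | 85.0% | 88.2% |

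For p = 0.5–0.7 the gap runs from 34.4 − 31.2 = 3.2 to 88.2 − 65.2 = 23.0 points in favour of MED-LFD. At p = 0.3–0.4 it is zero or slightly reversed. Odd counts favour MED-LFD more (at p = 0.6: 71.0% for k = 7 and 75.3% for k = 11).

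**Step 3. Correlated weeks, same setting.** With a probit random intercept, a person with standard normal effect u answers 'yes' with probability q(u) = Φ((Φ⁻¹(p) + √ρ·u)/√(1−ρ)), and P(AR) is the average of P(Bin(k, q(u)) ≥ m) over u. For p = 0.5–0.7 and k = 6–12 (even), the gap is about 3–11 points at latent correlation ρ = 0.3–0.5 and about 2–4 points at ρ = 0.8.

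**Step 4. Selection into phase 2.** Suppose phase 1 lasts four weeks, the condition for moving on is the same more-than-half rule, and those who do not move on count as not having AR. Then

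P(AR) = Σ over x = 3, 4 of P(Bin(4, p) = x) × P(Bin(k₂, p) ≥ m − x), with k₂ = 6 or 8 and m the threshold for 4 + k₂ recordings.

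At p = 0.6 and k₂ = 6: 0.3456 × 0.8208 + 0.1296 × 0.9590 = 0.408.

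| p | NICE | MED-LFD, 4+6 | MED-LFD, 4+8 |
|---|---|---|---|
| 0.5 | 31.2% | 22.0% | 21.3% |
| 0.6 | 47.5% | 40.8% | 40.9% |
| 0.7 | 65.2% | 62.0% | 62.5% |

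MED-LFD is now about 3–10 points lower. Under these assumptions it cannot be higher: meeting the phase-1 condition is the same event as AR in NICE, and further weeks can only remove people.

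**Step 5. Effect on the test.** With 54 per group, p = 0.6 and independent weeks, the approximate chance of a significant difference between equal diets is 11%, 23%, 38% and 51% for k = 6, 8, 10 and 12 without selection, and about 10% with selection, against a nominal 5%.

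**The case against.** The strongest objection concerns direction. A reader might infer that the rule is simply stricter for NICE and so inflates the MED-LFD result. The documents do not support that. The required share is higher in NICE, but a full MED-LFD series is planned only for participants who already had relief in phase 1. Step 4 shows the sign reversing if the others count as not having AR. The article states neither the exact condition for moving on nor how those who do not move on are classified. This objection stands, and no signed bias should be claimed.

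The size is also uncertain. The largest gaps need independent weeks and 10–12 recordings, and repeated answers from one person are unlikely to be independent. Strong correlation leaves only a few points. At k = 6 and p = 0.4 the arms coincide at 17.9%. A missed call changes the rule as well: with three recordings, NICE needs 2 of 3. All of this stands and limits the magnitude.

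Finally, AR is one of several secondary endpoints with no stated ranking, and the six-month question is the same in both arms. That limits the consequence but does not make the first-follow-up rates comparable. Reading the given period as each phase separately does not help either, because NICE has no period that matches reintroduction.

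**Conclusion.** The concern holds in a direction-neutral form. As written, AR at first follow-up is counted over periods of different length and content, and the resulting rates are compared as if they were alike. The restrictive phase has no stated length, but reintroduction alone exceeds four weeks, so the mismatch is present on any reading.

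How far equal diets would differ depends on assumptions that the document does not fix: the weekly chance of relief, the within-person correlation, the number of MED-LFD recordings, and the handling of those who stop after phase 1. Over the ranges examined, with p = 0.5–0.7, the result runs from about 23 points in favour of MED-LFD to about 10 points against it. With strong correlation and no selection it is only about 2–4 points. The issue is worth correcting before analysis. It does not touch the IBS-SSS endpoints through this rule, nor AR at six months.

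**What to change.** Define the between-arm AR comparison at first follow-up on the same weekly calls in both arms, weeks 1–4 from the start of the diet, with the same more-than-half rule. Apply it to all randomised participants, whether or not they go on to phase 2. Report later MED-LFD recordings descriptively, and keep the single six-month question for both arms. Equal diets then have equal expected AR rates, for example 47.5% in each arm at p = 0.6 with independent weeks and four calls answered.

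The weekly calls for these weeks are already planned in both arms, so no data collection or patient management changes. The cost is one of interpretation: this AR would describe weeks 1–4 and would no longer coincide with the MED-LFD visit at the end of reintroduction, where the other first-follow-up measures are taken. The endpoint should be labelled accordingly.

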#### 2.8.3. Adherence

Adherence to the diets will be assessed weekly by telephone, by asking the question: “How often did you follow your weekly diet?” and scored on a 5-point Likert scale (never, rarely, sometimes, most of the time, and every day).

### 2.9. Study Timepoints

Three study timepoints are anticipated: Baseline: Two to four days before intervention initiation; first follow-up: at 4 weeks following the introduction of the dietary plan for the NICE group and at the end of the reintroduction phase for the MED-LFD group, anticipated to last on average 6–8 weeks (2–4 days’ time window); second follow-up: at six months (1-week time window), as shown in Figure 1, which also illustrates the procedures to be performed at each timepoint.

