### 2.5. Consultations

After the initial consultation, participants will meet the same dietician on subsequent visits, physically or virtually. These visits are scheduled to occur up to four weeks after intervention initiation for the NICE group and six months after the first visit. In the MED-LFD group, visits are scheduled at the end of the restrictive phase to assist participants with implementing reintroduction, at the end of the reintroduction phase, and six months after the first visit.

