### 2.12. Exploratory Analyses

Aiming to explore the physiology mechanism implicated in the development of the positive effects of the MED-LFD in IBS symptoms management, we foresee the following mechanistic exploratory analyses in a subgroup of 40 participants (20 from each intervention group) who will provide stool samples at each study timepoint for gut microbiota analysis using metagenomics, and short-chain fatty acids (SCFAs)—acetate, butyrate, and propionate—the intestinal bacterial metabolites produced by fermented nondigestible carbohydrates [11], measurement using Gas Chromatography/Mass Spectrometry. In this subgroup, detailed measurements of the adherence to the diet will be assessed with three-day 24 h dietary recalls (on consecutive days, including a weekend day) twice by telephone contact. The first one at two weeks after interventions started, and the second six months after interventions started for both groups. The dietary recalls aim to calculate the number of consumed FODMAPs per day.

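### The first follow-up, one of two primary timepoints, falls at 4 weeks in NICE but at least 2 weeks later in MED-LFD, so the arms are compared at different elapsed times

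*Protocol article*

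**What the plan says.** All references are to the protocol article.

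- **Visit timing (2.9).** The first follow-up is "at 4 weeks following the introduction of the dietary plan for the NICE group and at the end of the reintroduction phase" for MED-LFD, with a window of 2–4 days. The second is at six months in both arms.
- **Role of the visit (2.10).** IBS-SSS change from baseline is primary, and the rate of at least a 50-point reduction is co-primary. Both are taken at both follow-ups.
- **Control diet (2.4.2).** "Participants in the control group will receive a weekly dietary plan for four weeks according to NICE guidelines".
- **Route to the MED-LFD visit (2.4.3, Second Phase).** "Participants experiencing adequate relief symptoms during phase 1 will proceed to phase 2". The length of the restrictive phase is not stated.
- **Dietician visits (2.5).** "In the MED-LFD group, visits are scheduled at the end of the restrictive phase to assist participants with implementing reintroduction". No IBS-SSS assessment is tied to that visit.
- **Adequate relief (AR) calls (2.8.2).** These are weekly for four weeks in NICE, and through the elimination and reintroduction phases in MED-LFD. AR needs positive answers in more than half of the recordings.
- **Analysis (2.11.3).** Arms are compared by Student's t-test and chi-squared test, with no term for elapsed time.

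**The concern.** Everyone enters with IBS-SSS above 175 (section 2.1), so scores may well move after baseline whatever the diet, through natural fluctuation and regression to the mean. A comparison between arms cancels that movement only if both arms are scored at the same distance from baseline. Here they are not, at a visit that carries both the primary and the co-primary endpoint. A common time trend would enter the estimated diet effect directly. The number of weekly relief calls before the visit differs in the same way.

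A second weakness follows from tying the visit to a diet phase. A MED-LFD participant without adequate relief in phase 1 does not start reintroduction, so the end of reintroduction never comes and the first follow-up has no date. In NICE the visit is at week 4 whatever the response. The limitations listed in section 3 do not mention the unequal timing.

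**Working it through.** **1. What the 6–8 weeks covers.** Section 2.9 places the MED-LFD visit "at the end of the reintroduction phase for the MED-LFD group, anticipated to last on average 6–8 weeks (2–4 days’ time window". Grammatically this could be the time to the visit or the length of the phase. The Second Phase text is specific: "During this phase (reintroduction), which will last for 6 to 8 weeks", and that phase follows the restrictive one. The two readings give:

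| Reading | MED-LFD, weeks from diet start | NICE | Gap |
|---|---|---|---|
| 6–8 weeks is total time | 6 to 8 | 4 | 2 to 4 weeks |
| 6–8 weeks is reintroduction alone, after restriction of 4 weeks (assumption) | 4 + 6 = 10 to 4 + 8 = 12 | 4 | 6 to 8 weeks |

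On either reading the expected gap is at least 2 weeks, more than a window of 2–4 days can absorb.

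**2. Whether the planned tests can separate time from diet.** By schedule, no NICE participant is scored at the MED-LFD time and no MED-LFD participant at week 4. Timing is almost fully tied to arm, so a t-test or chi-squared test returns the diet effect plus any timing effect.

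**3. The plan's sample-size figure.** From section 2.11.1: difference 100 − 59 = 41, SD 60, power 80%, α = 0.05 (taken as two-sided), 10% adjustment.

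n per arm = 2 × (1.960 + 0.842)² × 60² / 41² = 33.6, so 34. Then 34 / 0.9 = 37.8, so 38 per arm and 76 in total. The stated figure of 108 (54 per arm) is not reproduced. That is a separate matter on which this point does not depend. The stated 54 per arm is used below.

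**4. What a timing-only shift would do.** The documents give no drift rate, so the shift b is assumed.

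SE = 60 × √(2/54) = 11.55 points.

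With no diet effect, P(reject) = Φ(b/SE − 1.96) + Φ(−b/SE − 1.96). If the true difference is 41 and the shift runs against MED-LFD, power = Φ((41 − b)/SE − 1.96).

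| Shift b (points) | b/SE | Two-sided error, nominal 5% | Power, shift against MED-LFD |
|---|---|---|---|
| 0 | 0 | 5% | 94% |
| 5 | 0.43 | 7% | 88% |
| 10 | 0.87 | 14% | 77% |
| 20 | 1.73 | 41% | 44% |

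**5. Relief calls.** NICE has 4 weekly recordings; MED-LFD has 6 to 12, depending on the reading in step 1. More than half means at least 3 of 4, 4 of 6 or 7 of 12. With the same 60% weekly chance of relief in both arms and independent weeks (both assumptions), the binomial probability of achieving AR is 48%, 54% and 67%. Correlation between a person's weeks would shrink these differences.

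**The case against.** The strongest defence is that the trial compares two programmes, each scored at the end of its own course. Diet phase and dietician support belong to the randomised MED-LFD programme, so differences in them are not confounding. That stands for phase and support, but not for elapsed time or the number of outcome recordings, which belong to neither diet. The article does not give this rationale, and the six-month visit already compares the whole programmes at one common time.

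Several stronger readings are tempting but unsupported:

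- **Nothing at the first follow-up can be attributed to diet, and no analysis could help.** This goes too far. Unknown direction does not make a bias irremovable. A modelled time trend, for instance between the NICE scores at week 4 and six months, could adjust for timing under assumptions. The planned tests do not do so.
- **Drift accounts for about half of the planned effect.** Three points per week over 6 to 8 weeks would give 18 to 24 points, or 44–59% of 41. The same rate over 2 to 4 weeks gives 6 to 12 points, or 15–29%. No rate is documented, so neither range is a finding.
- **Response to restriction goes unmeasured.** AR is recorded weekly during elimination. What is missing is IBS-SSS and the other questionnaires at a time shared with NICE.
- **Contact is known to be heavier in MED-LFD overall.** The adherence calls in section 2.8.3 are weekly with no arm-specific end, so total calls cannot be compared. Only the AR schedule is explicit.
- **The stool samples and dietary recalls are mistimed.** They are exploratory, in 40 participants, and nothing requires recall and stool sampling to coincide.

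**Conclusion.** The concern holds for the first follow-up only. One of the two primary between-arm comparisons is made at unequal elapsed times: a gap of 2 to 4 weeks on one reading, or 6 to 8 weeks on the other if restriction lasts four weeks (assumed). The planned tests cannot distinguish a timing effect from a diet effect. The direction is unknown: longer follow-up may favour MED-LFD, while recent FODMAP challenges may count against it. The error rates and power figures above rest on assumed shifts. They show that a shift of 10 points, about a quarter of the planned 41, would already matter; they do not show that such a shift will occur.

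The visit is also undefined for MED-LFD participants who do not enter reintroduction. A reader might infer that they will be left out, so that MED-LFD is judged on responders alone. The article does not say so; it gives them no date.

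The six-month comparison is not affected by the unequal timing.

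**What to change.** 1. Define the first follow-up as the same number of weeks from diet start in both arms, for all randomised participants whatever their diet phase. Collect IBS-SSS and the other questionnaires then. In MED-LFD, use the end-of-restriction visit if it falls in that week, and otherwise collect remotely.
2. Count the AR calls used for the endpoint over the same weeks in both arms.
3. If a post-reintroduction score is kept, collect it at the same week in NICE.
4. Reconcile section 2.9 with the Second Phase text on what the 6–8 weeks covers.
5. If the visits cannot be aligned, make six months the sole primary between-arm timepoint and report the first follow-up descriptively.

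The cost is a protocol amendment, at most one remote questionnaire and some short calls. No extra participants are needed. The fallback in item 5 needs no new data collection.
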